
### Combined LI-BFR and resistance training protocol—current guidelines

Scott et al. [9] has provided evidence-based guidelines on optimal muscle hypertrophy and strength responses to LI-BFR training. This includes using cuff widths (~6 to 13.5 cm) for the legs and resistance training at 50 to 80% of occlusion pressure taken at rest; a detailed description of the technique used to establish occlusion pressure is provided in a later section (LI-BFR Group). BFR can be used with low-intensity exercise (~20–40% of 1 RM), utilising 50 to 80 repetitions per exercise, with occlusion maintained during inter-repetition rest periods of 30 to 45 s. Both single and multi-joint exercises can provide benefit and clinical populations are advised to complete two to three training sessions per week; however, training twice each day with BFR is possible. These guidelines will form the foundations of our LI-BFR training protocol.

### Generic lower-limb rehabilitation intervention

The total duration of treatment is 3 weeks, utilising 15-days of specific MDT exercise rehabilitation (Monday to Friday). There is no follow-up period, as the aim is to assess the feasibility and effects of the intervention(s) during the period of in-patient rehabilitation. A summary of the DMRC lower-limb MDT rehabilitation programme and treatment components is provided at Fig. 1 and Table 2, respectively. This generic treatment approach has been described elsewhere by Coppack et al. [49]. All participants will receive individualised programmes focussing on improving range of motion, balance, aerobic conditioning, manual therapy and education sessions. The generic MDT programme will be common to both groups with only the resistance training or LI-BFR intervention individualised to each participant dependent on group allocation. Additional information regarding each of these components is provided below.

**Table 2 Tab2:** Components of generic in-patient rehabilitation programme

Treatment modality	Treatment content	Treatment goals	Typical number of sessions per week
Individualised Exercise: led by ERI (45–60 min)	Strengthening exercises, active range of motion exercises, functional balance drills, gait drills, progressive coordination drills, non-weight-bearing aerobic/endurance exercise	Restore strength of major muscle groups of the lower-limb, improve core strength, increase joint range of motion, improve balance and neuro-muscular control, and improve muscle endurance.	3–4
Individualised physiotherapy (30–60 min)	Manual therapy techniques, muscle activation and timing patterns, active and passive range of motion exercises, advice on home exercise, gait re-education training	Improve quality and timing of movement, improve muscle strength, reduce pain, increase joint range of motion, induce relaxation, promote normal walking gait.	1–3
Group Exercise: led by ERI (45–60 min)	Group based circuit training that primarily involves high repetition muscular strengthening exercises targeting the whole body. May also include minor team games, recreational therapy, foam rolling, stretching, motor control, running re-education, cv	The same as the Individual exercise sessions, but also the promotion of group cohesion and social support	12
Hydrotherapy/swimming (30/45 min)	Non-weight-bearing aerobic exercise, strengthening exercises, active range of motion exercises, self-paced recreational swimming, progressive/assisted weight-bearing exercise and activity	Improve muscle strength, improve aerobic capacity, increase joint range of motion, improve confidence in weight bearing, induce relaxation, and promote enjoyment and fun.	1 hydro 3 swim
Individualised occupational therapy session (30–60 min)	Relaxation techniques, postural re-education, cognitive behavioural therapy techniques, self-help coping strategies, pain management.	Induce relaxation, promote behavioural change, control pain, correct/improve poor posture	0–3
Patient education (60 min)	Coping with pain, benefits of exercise, joint protection, anatomy and pathology of their lower-limb injury, nutrition.	Goal setting, activity modification, reduction of pain, promote behavioural change, weight management, improve knowledge of treatment options, improve ability to relax, improve knowledge of self-help techniques	4

### Stretching and range of motion exercise

Static and active stretching and foam-roller techniques will be employed to maintain the range of motion (ROM) required for optimal function. This forms part of routine clinical practice within lower-limb rehabilitation in the UK military.

### Neuromuscular control and functional balance exercise

Balance and proprioceptive exercises will be included to restore deficits and re-establish neuro-motor control. Progression will be applied by increasing the complexity and difficulty of the exercise, by reducing the base of support, adding dynamic movements on unstable surfaces and increasing the range through which the movement is performed. Support for neuromuscular training in lower-limb rehabilitation has been reported in the literature [50].

### Aerobic exercise

Participants will undertake light to moderate aerobic conditioning over the intervention period. In addition to the general health benefits conferred by aerobic exercise, moderate joint loading has been shown to be beneficial for joint health because of mechanosensitive chondroprotective pathways [51]. No study has described the optimal dose of aerobic exercise for patients undergoing lower-limb rehabilitation in terms of intensity, volume and duration. In this study, the supervising ERI will determine the nature of aerobic exercise (walking, cycling, swimming, cross-trainer) and progression in intensity based on individual examination finings and patient response to exercise.

### Manual therapy

Manual therapy techniques will be used to modify the quality and range of motion of soft tissue structures, and assist with pain relief. The manual therapy intervention will be prescribed individually for each participant on the basis of the physical examination findings, from a list of techniques including, trigger point massage, passive joint mobilisation, distraction and sustained stretches [49]. These techniques are commonly used in the management of injured military personnel at DMRC and delivered by their respective MSK physiotherapist.

### Education

Educating the patient on factors surrounding their treatment and the importance of regular exercise is a key component of the rehabilitation process at DMRC to optimise patient adherence to home or work-based exercise programmes. Education and advice will be a focus of the intervention and will include information on diagnosis and aetiology of their injury, rationale for treatment, the benefits of exercise, joint protection and activity modification strategies, pain management, coping with acts of daily living (sitting, driving, sleeping, work) and the importance of increasing physical activity levels in everyday life [49]. Unsupervised home-based prescription of BFR has not been investigated and therefore not recommended in the UK Defence best practice guidelines. Instead, the LIBFR group will be prescribed a conventional resistance training programme to perform upon discharge from the rehabilitation centre.

### Intervention group 1—LIBFR group

#### Determining limb occlusion pressure

The participant’s limb occlusion pressure will be determined during a one-off procedure prior to commencing the LI-BFR training programme. The participant lies in a semi-recumbent supine position on a treatment couch and a contoured 66 × 10 cm or 90 × 10 cm width blood pressure cuff (Schuco TourniCuff, Schuco International, Watford, UK) is placed around the most proximal part of each thigh. The length of the cuff (60 or 90 cm) will be selected based on the participant’s thigh girth, thereby ensuring sufficient overlap of the inflatable regions of the cuff to provide occlusion to the lower-limb. The cuff size will be recorded and then used for the entirety of that participant’s LI-BFR training programme. The posterior tibial or dorsalis pedis pulse is found with a MD2 vascular Doppler probe (Huntleigh Healthcare Ltd., Cardiff, UK). The wide contoured tourniquet will rapidly be inflated using a PTSii portable tourniquet system (Delfi Medical Innovations, Vancouver, Canada) to a pressure of 250 mmHg [52] so that the audible pulse is lost. If the pulse is not lost at 250 mmHg, then the cuff will be inflated in increments of 10 mmHg until the pulse is abolished. The cuff will be deflated in increments of 10 mmHg until the pulse is found again. This provides an estimate to the nearest 10 mmHg. The cuff will then be fully deflated. After a 30 s rest, the cuff will be inflated to the estimate pressure + 10 mmHg. It will then be deflated more slowly in increments of 5 mmHg, so the occlusion pressure can be determined to the nearest ±5 mmHg. 60% of this limb occlusion pressure is calculated to be used as the tourniquet pressure during the LI-BFR intervention [9]. Subsequent limb blood occlusion pressure assessments will be performed on day 7 and the final training day to measure potential changes in occlusion pressure over time. Any measured changes in pressure on day 7 will not influence the cuff pressure used during the trial.

### LI-BFR exercise protocol

Participants will perform low intensity resistance training combined with blood flow restriction using two exercises in sequence: (1) bilateral leg press using a Leg Press Machine (Pulse Fitness, Congleton, UK), and (2) bilateral knee extensions using a Leg Extension Machine (Pulse Fitness, Congleton, UK) (see Fig. 3).

**Fig. 3 Fig3:**
[figure not shown]
Low intensity blood flow restriction (LI-BFR) exercises: **a** leg press, **b** knee extension

Prior to exercise, each participant will undergo a standardised 5 min progressive warm-up on a stationary bike (Wattbike Ltd., Nottingham, UK). Wide contoured blood pressure cuffs will then be placed around the most proximal part of each thigh and inflated using a PTSii portable tourniquet system to 60% occlusion pressure. Participants will then perform 4 sets of 30, 15, 15 and 15 repetitions (75 repetitions in total) at 30% of their predicted 1RM, assessed during their 5RM muscle strength assessments with an inter-set interval of 30 s (see secondary outcome measures below for a detailed description of the 5RM muscle strength assessment protocol). To ensure consistency of lifting between patients, a metronome is set at 60 bpm, with 1 s for the completion of the concentric phase, no pause followed by a 1 s eccentric phase of the lift (1:0:1 tempo).

The inflation pressure will be maintained for the duration of the exercise and then deflated for 3 min to allow the participant a small recovery period and to move to the next exercise/equipment station. It will then be re-inflated to the target 60% occlusion pressure and the second exercise station (leg extension) will commence. Therefore, the length of time induced to restricted blood flow will be 4 min per exercise and 8 min per training session. Training will be performed twice daily, in the morning (between 08:00 and 09:30) and afternoon (between 14:00 and 15:30) from Monday to Thursday and once on Friday morning. Over the 15 days of rehabilitation, MDT clinical assessments will be carried out on the first and last day of an admission. This allows a maximum of 23 LI-BFR training sessions over a total period of 13 treatment days. Daily LI-BFR sessions will always be separated by interludes of at least 5 h. Assuming patients adapt over the 3 week residential programme, the 1RM is expected to increase and therefore even when exercising at 30% 1RM, we would expect to increase the weight lifted by small increments (e.g. 2.5 kg increase per week). Any increase in weight lifted will be at the discretion of the exercise rehabilitation instructor (ERI) and participant, and training load (the number of repetitions and load lifted) for each session will be monitored and recorded accordingly.

### Intervention 2 conventional resistance training

Participants will engage in conventional load bearing resistance training, typically consisting of four sets of three exercises (deadlift, back squat and lunges) performed three times per week. A gradual and timely exercise progression is determined by the ERI based upon participant feedback, re-assessment and individual response to training. It should be noted that despite an abundance of information on the implementation of strength and conditioning principles with healthy participants, investigation regarding the application of these principles in rehabilitation programmes is lacking [53]. Therefore, a relatively conservative initial dosage is chosen that should allow a short period of adaptation whilst controlling for pain, thereby promoting exercise adherence. Patients will be educated on correct movement patterns before loading to volitional fatigue. Repetitions per set are typically six to eight and tailored to the individual needs of the patient with rest intervals between each set approximately 3 min. The dosage for strengthening exercises in this protocol aims to meet the ongoing challenge of designing treatment programmes that facilitate neurological and muscular adaptations whilst concurrently accommodating biological healing, recovery, and the safety of the patient. The justification for the initial dosage of four sets of six to eight repetitions takes account of the evidence suggesting pain provoked by exercise has been shown to reduce adherence to exercise in rehabilitation programmes [54]. The load lifted is a reflection of their best effort taking into account each individual’s respective limitations due to injury.

### Outcome measures

All outcome measures are to be assessed at baseline and upon completion of 3 weeks in-patient rehabilitation. Pain response and training load will be recorded over several time points during the BFR intervention (Fig. 2). The authors acknowledge that due to the likely interference effect of a pain response, performing a ‘maximum effort’ physical task in a lower-limb injured cohort is unlikely to yield a true measure of MSK performance. It is more accurate to describe outcome scores as providing an ‘indication’ of participant performance and progression. We will highlight this as a potential weakness in our study but feel this is a challenge in the measurement of muscle force/strength in all MSK injury research. All outcomes measured will be implemented and recorded based upon a best effort at the time of assessment.

### Descriptive data

Personal and demographic characteristics including age, stature, body mass, body mass index (BMI), gender, duration of symptoms, previous injuries, previous treatments, medication use, military occupation, duration of military service, smoking and drinking habits will be obtained during the initial participant assessment or obtained via electronic medical notes using the Defence Medical Information Compatibility Program (DMICP).

### Primary outcome measure: feasibility and acceptability of LI-BFR intervention

The main focus of this study is feasibility and acceptability for recruitment, retention and measurement of the LI-BFR intervention. Recruitment rates will be measured as the rate of eligible participants invited and consenting into the study. Acceptability of allocation/randomisation procedures will be assessed by examining the reasons for drop-out in any discontinuing participants and by comparing attrition rates between groups. Session adherence rates will be recorded to provide a measure of compliance with the intervention. Strengths, weaknesses and safety of LI-BFR intervention will be assessed by qualitative interviews with the project supervisor, lead exercise rehabilitation instructor, participant feedback and examination of any adverse event reports. We will also aim to provide an estimate of the recommended sample-size for a fully-powered future RCT [55].

### Secondary outcome measure: muscle cross sectional area (CSA) and volume

Thigh muscle cross sectional area (CSA) (cm^2^) and volume (cm^3^) will be assessed prior to and 1 day following the subject’s rehabilitation training programme, using magnetic resonance imaging (MRI) with a GE Sigma scanner 1.5 T (General Electric, Wisconsin, USA), in accordance with the method previously described by Abe et al. [56]. A T1-weighted, spin-echo, axial plane sequence will be obtained with continuous transverse images from the greater trochanter to the lateral condyle of the femur with a 1.0 cm slice thickness and no inter-slice gap. If this distance exceeds 50 cm, two separate sequence acquisitions will be required with a triglyceride skin marker used for sequence co-registration. The MRI data will be transferred onto a study laptop computer for analysis by a UK Defence Consultant Radiologist, using specially designed image analysis software (TomoVision Inc., Montreal, Canada) [57]. For each slice on the injured limb, quadriceps and hamstring muscle compartment CSA (cm^2^) will be measured and muscle compartment volumes calculated (cm^3^). In participants with bilateral pathology, one leg will be randomly selected for muscle analysis. The coefficient of variation (CV) for this measurement technique has been demonstrated to be less than 1% [56]. Repeat MRI assessments will be performed 24 h after the participant’s final LI-BFR training session.

### Secondary outcome measure: muscle strength

Unilateral muscle strength will be assessed using a dynamic 5 RM test performed on the knee extension and leg press machines (Pulse Fitness, Congleton, UK). Following a general warm-up on a stationary bike for 5 min, subjects will perform a 10-repetition warm-up on the knee extension and leg press respectively. An initial resistance is set by the supervising ERI based upon the result of a clinical assessment, pain intensity and participant feedback. The resistance is then adjusted and test repeated until the participant is unable to complete five repetitions. The baseline 5RM is then recorded by the supervising ERI. Subjects will have 3 min rest between each attempt. This procedure follows established and widely used guidelines [58].

### Secondary outcome measure: functional performance assessment

Functional ability will be assessed using the following standardised outcome measures used in the current best-practice care pathway at DMRC. These tests will be conducted and recorded by an experienced supervising therapist.

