**Methods:**

This is a single-blind randomised controlled feasibility study. A minimum of 28 lower-limb injured UK military personnel, aged 18 to 50 years, attending rehabilitation at the UK Defence Medical Rehabilitation Centre (DMRC) will be recruited into the study. After completion of baseline measurements, participants will be randomised in a 1:1 ratio to receive 3 weeks (15 days) of intensive multidisciplinary team (MDT) in-patient rehabilitation. Group 1 will receive conventional resistance training 3 days per week. Group 2 will perform twice daily LI-BFR training. Both groups will also undertake the same common elements of the existing MDT programme. Repeat follow-up assessments will be undertaken upon completion of treatment. Group 2 participants will be asked to rate their pain response to LI-BFR training every five sessions.

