### Study design

This is a parallel group, two-arm, assessor-blinded randomised controlled feasibility study. It is a two (group) by two (time) repeated measures design. Outcome measurements will be assessed at baseline and 3-weeks. The study protocol has been developed in accordance with the Standard Protocol Items: Recommendations for Interventional Trials (SPIRIT) guidelines [48]. The overall study design is illustrated in Fig. 2.

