### Randomisation and blinding

Potential participants will be referred from their parent military unit by a physiotherapist or medical officer. Prior to admission to DMRC, the case records of individual patients scheduled for a lower-limb rehabilitation course will be reviewed by a specialist rehabilitation consultant ([name]). Those who meet the preliminary inclusion criteria will be contacted via telephone by a member of the research team to discuss their possible inclusion in the study. Potential participants will be sent an information pack consisting of the patient information sheet (PIS) and an accompanying consent form. Upon admission to DMRC Headley Court, potential participants will undertake a comprehensive musculoskeletal examination by a specialist consultant and experienced musculoskeletal physiotherapist where a secondary screening will confirm the patient’s eligibility to enter the study. Participants meeting the eligibility criteria, who have read and understood the PIS and volunteer to participate will return a signed informed consent form, before being randomly assigned to one of the two study groups. A block randomisation method will be used to randomise participants into groups that result in equal sample sizes. Our decision to employ a simple form of block randomisation is because (a) we want to ensure an equal number of participants are assigned to each group during a finite, time-limited period for data collection, (b) we already have a homogenous participant group with standardised prognostic factors, and (c) we will not be undertaking formal statistical testing. A plain language statement will inform participants that they have an equal chance of receiving the LI-BFR or conventional resistance training intervention. A sealed envelope will be opened to reveal group allocation by an independent administrator not involved in the recruitment, treatment or assessment of study outcomes. Group allocation will be documented and communicated to the supervising therapists by the independent administrator. Prior to the study, all treating staff will have received a briefing on the randomisation process and specific intervention for each treatment group, in line with the study protocol. It is not possible to blind participants to treatment allocation in this study. The clinical staff supervising both groups will be, by necessity, un-blinded. We will use trained blinded outcome assessors to measure and record the outcome scores in this study. A diagrammatic description of the study design can be found in Fig. 2.

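### The plan promises blinded outcome assessors but assigns the functional tests to supervising therapists, the role it says is told the allocation

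*Protocol article*

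**What the plan says.** The protocol article describes its blinding in four places.

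- **Label.** *Study design* calls the trial a "parallel group, two-arm, assessor-blinded randomised controlled feasibility study". The abstract uses the term single-blind. Participants cannot be blinded, according to *Randomisation and blinding*, so the outcome assessors are the only blinded party the article names.
- **General rule.** *Randomisation and blinding* states: "We will use trained blinded outcome assessors to measure and record the outcome scores in this study". It makes no exception for any outcome.
- **Who knows the arm.** The same section says "Group allocation will be documented and communicated to the supervising therapists by the independent administrator" and adds: "The clinical staff supervising both groups will be, by necessity, un-blinded".
- **Who tests.** *Secondary outcome measure: functional performance assessment* says of the tests it introduces: "These tests will be conducted and recorded by an experienced supervising therapist". *Secondary outcome measure: muscle strength* has the supervising exercise rehabilitation instructor (ERI) choose the starting resistance for the 5RM test and then says: "The baseline 5RM is then recorded by the supervising ERI".

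The abstract places randomisation after the baseline measurements. *Outcome measures* schedules every outcome at baseline and again at the end of the 3 weeks.

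**The concern.** The role named as tester for the functional outcomes carries the same title as the role that receives the allocation. If the article is followed as written, the 3-week functional tests would be run by someone who knows the participant's arm, although the design is described as assessor-blinded.

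These outcomes leave room for such knowledge to matter. In the hip extension test the examiner holds the dynamometer and supplies the resistance by hand, and the best of four attempts is kept. *Outcome measures* itself describes all scores as best-effort indications of performance rather than true maxima.

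Two things are at stake. First, comparing the arms on muscle strength is part of the secondary aim, with walk/run and balance measures also assessed, and the 95% confidence intervals are to inform the sample size of a definitive trial. A tester effect that differs between arms would enter those estimates. Second, *Statistical analyses* says the pilot serves to test the study procedures. Blinded assessment is one such procedure, and a pilot that does not carry it out cannot show that it works in this setting.

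**Working it through.** No arithmetic applies: the question is who measures what, when, and with what knowledge. The plan makes no formal sample size calculation, so there is no stated figure to reproduce. The check sets the sections side by side.

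**Step 1: who knows the allocation at 3 weeks.** Supervising therapists are told it directly, and staff supervising either group are declared unblinded (*Randomisation and blinding*). ERIs share decisions on load increases in the blood flow restriction arm (*LI-BFR exercise protocol*) and determine progression in the conventional arm (*Intervention 2 conventional resistance training*). An ERI supervising a participant therefore knows the arm by then.

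**Step 2: who is named as tester, by outcome.**

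| Outcome | Tester named | When | Conflict with the blinding rule? |
|---|---|---|---|
| Isometric hip extension strength | Supervising therapist | Start and end of the 3 weeks | Yes, on the wording |
| Multi-stage locomotion, figure of 8, Y-balance | Supervising therapist | Baseline and 3 weeks | Yes, on the wording |
| 5RM leg press and knee extension | Supervising ERI sets the starting load and records the baseline value | Recorder named for baseline only | Not stated; inferred for 3 weeks |
| MRI cross-sectional area and volume | Consultant radiologist | Before and after the programme | None stated; the reader's blinding is not stated either |

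**Step 3: does timing remove the conflict?** At baseline it does, because randomisation follows and there is no allocation to know. At 3 weeks it does not. The sentence assigning the functional tests is not limited to baseline, and *Isometric muscle strength proximal to the cuff* gives both measurement times.

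**Step 4: the 5RM.** Only one 5RM procedure is described and no other tester is named for follow-up, so it is natural to read the ERI as tester on both occasions. But the one explicit recording sentence concerns a value taken before randomisation, and that act breaks no blind. For the 3-week value, the general promise of blinded assessors is not expressly contradicted.

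**Step 5: what depends on these outcomes.** All are secondary. The primary outcomes are recruitment, retention, adherence, acceptability and safety. The progression criteria are 80% of target recruitment over 6 months, and 80% completion of the intervention and of outcome measurement. None of these depends on whether the tester is blinded.

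**The case against.** The best defence is that *Randomisation and blinding* governs the matter and is explicit, while supervising therapist in the functional section may simply mean the person who supervises the test. The article never says that a therapist tests a participant whom he or she treats. This has some force: it rules out asserting as fact that the follow-up tests will be unblinded. It does not remove the inconsistency, because the article uses the same title for the staff who receive the allocation and draws no distinction between the two uses. If a different person was meant, a sentence is needed to say so.

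A second defence is that this is a feasibility study with descriptive, exploratory analysis and no formal between-group test. That stands as a limit on severity. It does not dispose of the point, since the estimates and intervals are still meant to feed the planning of the next trial.

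A third is that the locomotion test leaves the tester little discretion: speed is set by audio cues, instructions are recorded, and there is a stopping rule of three consecutive failures. That is fair. The room for tester influence differs between tests, and the hand-held dynamometer is the clearest case.

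Three stronger readings are tempting, and the documents do not support them:

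- A reader might infer that the 3-week 5RM is recorded by unblinded staff. The article names the ERI as recorder at baseline only. The baseline value is also the basis for the training load in the blood flow restriction arm, which may be why the ERI records it.
- A reader might infer that MRI is the one outcome that is safely blinded. The MRI section does not say that the radiologist is blinded; that rests on the same general promise.
- A reader might take the test-retest variation of under 10% cited for the dynamometer as a guide to the size of the bias. It describes repeat-measurement variation for one device. It says nothing about a systematic shift from knowing the arm.

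**Conclusion.** The contradiction is real and lies in the current text. For the four functional tests, the blinding rule and the sentence naming the tester cannot both be followed if supervising therapist has the same meaning in both sections, and nothing in the article suggests otherwise. For the 5RM, unblinded follow-up testing is a reasonable inference but is not stated.

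The consequence is possible bias in descriptive between-arm estimates and their confidence intervals for secondary outcomes, and a design label that may claim more than the procedures deliver. The size of any bias cannot be given: the documents contain no figure that bears on it. The primary feasibility outcomes and the progression criteria are untouched. A should-fix, not an obstacle to the study's main purpose.

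**What to change.** Reconcile *Randomisation and blinding* with the muscle strength and functional performance sections:

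1. State that the 3-week 5RM, hip extension, locomotion, figure of 8 and Y-balance tests are run and recorded by the blinded assessors already promised, meaning staff who have not been told the allocation and do not treat that participant.
2. State that participants will be asked not to disclose their group to the assessor.
3. State whether the MRI reader is blinded.
4. If point 1 cannot be met for some outcomes, limit the assessor-blinded description to the outcomes for which it holds, and report the others as assessed unblinded.

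Baseline testing can stay as it is, since it precedes randomisation. The change adds no commitment beyond the one the article already makes. Its cost is a few sentences and the rostering of follow-up tests. The article does not describe staffing, so how easy the rostering would be cannot be judged from it; point 4 covers the case where it proves impractical.
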